### Endpoints

The primary endpoint of the study will be the proportion of patients developing at least an irAE at week 48 after the initiation of ICI therapy. An irAE was defined as any symptom, sign, syndrome, or disease caused by an immune-activating mechanism during the administration of an ICI once other causes such as an infectious disease or tumor progression have been ruled out.

Key secondary endpoints will be irAE-free survival, progression-free survival, cancer-related survival and overall survival. Other secondary outcomes will be proportion of ICI withdrawal due to the occurrence of irAEs, time to autoantibody appearance and number of positive autoantibodies included in the panel at week 48 after the initiation of ICI therapy.

### Study Design and Ethical Considerations

The protocol of the AUTENTIC study was designed in accordance with the Strengthening the Reporting of Observational Studies in Epidemiology guidelines. Accordingly, a multicenter observational prospective cohort study was designed with the participation of the following hospitals of the north of Spain: Araba University Hospital (Vitoria-Gasteiz), Navarra University Hospital (Pamplona), Galdakao University Hospital (Galdácano), Donostia University Hospital (San Sebastián) and San Pedro University Hospital (Logroño).

This study will be conducted in accordance with the Good Clinical Practice guidelines of the International Council for Harmonization (ICH) E6, the principles of the Declaration of Helsinki, and local regulations. Informed consent will be obtained from all participants before their enrollment. The study protocol has been reviewed and approved by the Ethical Committee of the Basque Country [code: PI2018106 (EPA-SP)] and the Spanish Agency of Medicines and Medical Devices (code: ILB-NIV-2018–01). The study has been registered in ClinicalTrials.gov (NCT03868046).

### Setting and Duration

The current study will consecutively enroll patients diagnosed with different types and stages of solid organ malignant tumors who are candidates for treatment with ICIs. In the setting of outpatient clinics, patients will be recruited by the medical oncologists responsible for their care in one of the participating hospitals. Recruitment will continue until the desired sample size is reached (see “*Study size calculation*” section). The autoantibody panel under study will be performed when the whole cohort reaches week 48 of follow-up from the time of inclusion, which will coincide with the ICI initiation date. Patients lost to follow-up will be censored at the time of their last follow-up.

### Participants

All patients diagnosed with a solid organ malignant tumour of any stage amenable to ICI therapy according to current guidelines are potentially eligible to participate. Patients will be included by the medical oncologists in charge in the outpatient clinic setting.

The patients must meet all the following inclusion criteria:1) Initiation of treatment with an ICI or a combination of ICIs2) ICI naïve status, though those treated in the past with other systemic therapies for cancer, such as chemotherapy or tyrosine-kinase inhibitors, may be included3) Provision of written informed consent.

Exclusion criteria will be the following:1) Life expectancy of less than 3 months from the start of ICI therapy2) Contraindication to ICI therapy: proven hypersensitivity or history of anaphylactic allergic reactions secondary to ICIs, active severe autoimmune disease, or poor performance status (Eastern Cooperative Oncology Group score ≥ 3)3) Active immunosuppressive treatment: prednisone at doses >10 mg/day or equivalent (e.g., 1.5 mg/day of dexamethasone), azathioprine, methotrexate, mycophenolate, cyclophosphamide, rituximab, leflunomide, anti-tumor necrosis factor agents (infliximab, etanercept, adalimumab, golimumab), or abatacept, among others.

### Follow-Up Methods

Once enrolled in the study, patients will be monitored following standard recommendations. In accordance with clinical practice guidelines (Schneider et al., 2021; Schneider et al., 2022), all patients will be assessed in a treatment planning visit at baseline. In this initial visit, attending physicians will take a detailed personal and family history focused on ADs, chronic infectious and organ-specific diseases, and conduct a physical examination. In addition, to guide their care, patients will undergo a baseline blood test including a complete blood count, measurement of glucose and thyroid stimulating hormone (TSH) levels and lipid profile, renal and liver function tests, coagulation tests, and serological tests for hepatitis B and C viruses and HIV.

The frequency of follow-up will depend on the treatment schedule of each specific ICI, discretion of the attending physician and occurrence of complications (irAEs, non-immune-related toxicity, infections). All patients will have direct telephone access to the investigators in order to report early symptoms potentially related to the occurrence of irAEs*.* Treatment schedules of the ICIs will be classified into every 2 or 3 weeks up to week 12; thereafter, drug administration may be spaced out to every 4 or every 6 weeks, respectively, according to the drug data sheets.

Two types of blood samples will be taken for research purposes only: ordinary samples, defined as those drawn routinely as scheduled (Figure 1 and Figure 2), and extraordinary samples, defined as those taken at the time an irAE is detected. As far as possible, ordinary blood samples will be collected at the same time as blood draws for medical purposes before the administration of each ICI dose, in accordance with the study schedules (Figures 1, 2).

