### Variables

Patients included in the study will be identified by a numerical code. In this way, the data collected by researchers will not include personal information, safeguarding patient confidentiality. The transmission, processing, and dissemination of personal data from all the participating patients will be handled in accordance with Regulation (EU) 2016/679 of the European Parliament and of the Council of 27 April 2016 on the protection of natural persons regarding the processing of personal data and the free movement of such data, i.e., the General Data Protection Regulation.

Study data will be entered into an electronic database to which all participating hospitals will have centralized access, and which will comply with all data protection requirements.

Dependent variable: occurrence of irAEs.

An irAE is defined as any symptom, sign, syndrome, or disease caused by an immune-activating mechanism during the administration of an ICI once other causes such as an infectious disease or tumor progression have been ruled out.

Other descriptive variables related to irAEs:• Description of symptoms related to the irAE• Type: organ-specific or systemic (≥ 2 organs affected)• Description of the involved organ• Syndrome/disease: Sjögren’s syndrome, sarcoidosis, systemic vasculitis, systemic lupus erythematosus, etc.• Severity, according to Common Terminology Criteria for Adverse Events v. 5.0• Date of diagnosis of the irAE• Treatment used for the irAE: non-steroidal anti-inflammatory drugs, glucocorticoids, immunosuppressive drugs other than glucocorticoids• ICI dose reduction: yes/no• ICI withdrawal: yes/no; if yes: temporary/permanent.

Independent variables: the following potential predictors of irAEs will be collected and analyzed: Epidemiological data: date of birth, sex, ethnicity.

General clinical data:• Smoking and alcohol use• Comorbidities: arterial hypertension, hypercholesterolemia, diabetes mellitus, cirrhosis/liver failure, renal insufficiency, thyroid dysfunction• Chronic infections: hepatitis B, hepatitis C, HIV infection• Autoimmune diseases prior to ICI initiation• Type of previous autoimmune disease (description)• Eastern Cooperative Oncology Group performance status score• Body mass index (in kg/m^2^).

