### Management of Potential Bias

The inclusion of patients with previous ADs could be influenced by attending physicians’ concern about inducing irAEs, and this could lead to a biased representation of the population eligible for the study. Researchers will encourage oncologists to include patients with ADs in remission on a case-by-case basis.

To minimize a detection bias arising from a higher level of suspicion of irAEs in autoantibody-positive patients, the autoantibody panel under study will be performed and the results analyzed after the whole cohort reaches week 48 of follow-up. On the other hand, for ethical and practical reasons, the autoantibody results from the extraordinary samples taken for medical purposes will be available to the attending physicians. Nonetheless, the laboratory staff involved in the detection and interpretation of autoantibodies will always be unaware of the clinical status of each patient.

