Survival will be assessed using a Kaplan-Meier analysis and compared between groups using the log-rank Mantel-Cox test. A subgroup analysis according to tumour type and extent of cancer (local, advanced, and metastatic disease) will be performed to assess survival outcomes*.* A multivariate analysis using logistic regression and Cox regression will be performed to detect factors associated with the occurrence of irAEs. Applying a manual backward stepwise procedure, a multivariate model will be constructed from variables that either have a p-value of less than 0.10 in the univariate analysis or are considered relevant to the dependent variable on the basis of previous studies (e.g., sex and age of patients, type of ICI). Variables not reaching statistical significance will be dropped from the final predictive model. The sensitivity, specificity, positive predictive value, negative predictive value, and probability ratios with their corresponding 95% confidence intervals of the model will be calculated. The diagnostic accuracy of the predictive model inferred from the logistic regression model will be described with the area under the receiver operating characteristic curve.

Two-sided hypothesis tests will be performed, and the significance level will be set at 5%. The statistical analysis will be conducted using IBM SPSS Statistics software version 27.0 (Chicago, IL).

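### irAEs of any grade are looked for at a frequency that differs by drug schedule and physician choice, so estimates for drug or regimen, and possibly prior autoimmune disease, can be distorted in either direction

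*Protocol article*

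**What the plan says.** **Follow-up.** Follow-Up Methods sets no common clinical visit grid: "The frequency of follow-up will depend on the treatment schedule of each specific ICI, discretion of the attending physician and occurrence of complications". In the first 12 weeks doses come at 2-week or 3-week intervals. For the later period the section says: "thereafter, drug administration may be spaced out to every 4 or every 6 weeks, respectively, according to the drug data sheets". At the baseline visit "attending physicians will take a detailed personal and family history focused on ADs", so the physician who has discretion over follow-up knows the autoimmune history.

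**Endpoint.** The primary endpoint (Endpoints) is the "proportion of patients developing at least an irAE at week 48 after the initiation of ICI therapy". The definition covers any symptom, sign, syndrome or disease of immune cause arising while an ICI is being given. Grade is only a descriptive variable (Variables): "Severity, according to Common Terminology Criteria for Adverse Events v. 5.0".

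**Predictors.** ICI class, monotherapy or combination, prior autoimmune disease, comorbidities and ECOG status are listed as potential predictors (Variables). A variable may enter the multivariate model with a univariate p-value below 0.10, or if variables of its kind "are considered relevant to the dependent variable on the basis of previous studies (e.g., sex and age of patients, type of ICI").

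**Safeguards.** Management of Potential Bias delays the panel until the whole cohort reaches week 48, "To minimize a detection bias arising from a higher level of suspicion of irAEs in autoantibody-positive patients". All patients have direct telephone access to the investigators. Research blood is drawn at weeks 0, 2 or 3, 6, 12, 24, 36 and 48, together with clinical draws (Ordinary Samples and Study Schedules).

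**The concern.** An endpoint that counts mild events depends on how often someone asks or tests. Here the frequency of looking is tied to characteristics that are also candidate predictors, above all the drug received. The first primary objective is to identify predictive factors, and the second evaluates the model built from them. If some patients are questioned more often, more of their mild irAEs will be recorded, and recorded earlier. A difference between drugs or regimens may then reflect surveillance, or surveillance may hide a real difference. irAE-free survival and the Cox model use the date of detection, so they are exposed even where an event is only found later and not missed. The protocol recognises that unequal suspicion biases irAE detection but closes only one route to it, knowledge of autoantibody results.

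**Working it through.** **1. The plan's own numbers.** The sample-size section gives 70 irAE cases at 25% incidence: 70 / 0.25 = 280, that is 70 cases and 210 non-cases. Adding 5% gives 280 × 1.05 = 294, as stated. This point disputes no figure; 280 patients and 25% are used below.

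**2. Dosing contacts after baseline**, from the intervals in Follow-Up Methods, for a patient treated to week 48:

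| | Weeks 0–12 | Weeks 12–48 | Total |
|---|---|---|---|
| 2-weekly, then 4-weekly | 12/2 = 6 | 36/4 = 9 | 15 |
| 3-weekly, then 6-weekly | 12/3 = 4 | 36/6 = 6 | 10 |

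The ratio is 15/10 = 1.5. Counting week 0 as well gives 16 versus 11. If neither schedule is spaced out, 48/2 = 24 versus 48/3 = 16, again 1.5. Spacing out is optional, so mixed cases occur: 2-weekly spaced against 3-weekly not spaced is 15 versus 4 + 36/3 = 16 (ratio 0.94), and the reverse is 24 versus 10 (ratio 2.4). The gap therefore also depends on local choice.

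**3. Which drugs sit where** (Ordinary Samples and Study Schedules; classes from Variables):

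| Class or regimen | 2-weekly | 3-weekly |
|---|---|---|
| Anti-PD1 | nivolumab | pembrolizumab |
| Anti-PD-L1 | avelumab, durvalumab | atezolizumab |
| Combination with anti-CTLA4 | none | ipilimumab + nivolumab |

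Schedule varies within both single-agent classes, so a comparison of anti-PD1 with anti-PD-L1 is only weakly exposed. Comparisons between individual drugs are fully exposed. The scheduled ipilimumab combination lies wholly in the less-visited group, so against 2-weekly drugs its risk would tend to be understated.

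**4. Illustration.** The documents give no detection rates; those below are assumptions. True risk is 25% in both groups, with 140 patients each (280/2). Observed risks are a = 0.25 with full detection and b = 0.25 × d with detection d. The false odds ratio is [a/(1 − a)] / [b/(1 − b)].

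The chance of a significant result in that direction is Φ[(a − b − z·s0)/s1]. Here s0 is the pooled and s1 the unpooled standard error of the difference, and z = 1.96 for p < 0.05 or 1.645 for p < 0.10. For d = 0.80: s0 = 0.0499, s1 = 0.0498, (0.05 − 1.96 × 0.0499)/0.0498 = −0.96, giving 17%.

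| d | b | False OR | Chance p < 0.05 (nominal 2.5%) | Chance p < 0.10 (nominal 5%) | Cases found, 140(a + b) |
|---|---|---|---|---|---|
| 0.90 | 0.225 | 1.15 | 7% | 12% | 66.5 |
| 0.80 | 0.200 | 1.33 | 17% | 26% | 63 |
| 0.70 | 0.175 | 1.57 | 33% | 46% | 59.5 |

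Seen from the less-watched group, the same distortion is 1/1.15 = 0.87, 1/1.33 = 0.75 and 1/1.57 = 0.64. That is the direction that would apply to the 3-weekly combination.

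**The case against.** The strongest reply is that this is an observational cohort under standard care, where visits follow the drug, and that the protocol already equalises much of the contact. All patients can telephone with early symptoms, and both schedules share almost the same sampling weeks. Over a cumulative 48-week endpoint, a gap of 2 versus 3 or 4 versus 6 weeks would mostly delay the dating of a persisting irAE, not lose it.

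Much of this stands. The contact ratio cannot be read as a detection ratio, and no passage shows how many events would be missed. Two parts do not remove the problem. Telephone access is initiated by the patient and does not equalise active questioning. The sampling weeks carry no stated irAE assessment, and the sample is not taken when a dose is delayed for a reason other than an irAE.

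A reader might infer more than the documents support:

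- *That the panel's accuracy is compromised.* Physicians do not know the ordinary-sample panel results during follow-up, and a subgroup analysis by prior autoimmune disease is planned, so any leak is indirect and limited. Panel results from extraordinary samples are visible, but only once an irAE has been detected.
- *That ICI type will look falsely predictive.* Step 3 shows mixing within classes, and understatement for the combination.
- *That hospital will appear as a predictor.* No centre variable is listed.
- *That patients with autoimmune history will be seen more often.* Discretion allows it, but nothing says so.
- *That visits triggered by a first irAE inflate the endpoint.* They cannot change whether a patient has at least one; only schedule, discretion, non-immune toxicity and infections matter there.

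**Conclusion.** The point holds as a design weakness worth correcting. Unequal ascertainment follows from what the protocol states about follow-up, and it is linked to candidate predictors while the endpoint has no grade threshold. The affected results are estimates for individual drug or regimen, possibly prior autoimmune disease, and the timing of mild irAEs in irAE-free survival and Cox models. The direction is not fixed.

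The 1.5-fold difference in dosing contacts comes from the stated intervals and assumes treatment to week 48 with both schedules spaced out, or neither. The size of the bias cannot be derived: odds ratios of 1.15 to 1.57, or 0.87 to 0.64 in the other direction, rest wholly on assumed detection rates of 90% to 70% against full detection and on an even split of patients. The sample size is not in question.

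**What to change.** 1. Apply the same short irAE checklist to every patient at the existing ordinary sampling weeks (2 or 3, 6, 12, 24, 36, 48), by telephone where no visit occurs. Routine clinical visits stay as they are.
2. Add one field recording whether each irAE was found at a scheduled check or at an extra contact.
3. Add a sensitivity analysis of the predictors limited to irAEs that depend least on surveillance: CTCAE grade 2 or higher, or leading to treatment or ICI withdrawal. Severity, irAE treatment and withdrawal are already collected.
4. Flag irAEs found after the ICI has stopped and analyse them separately, unless the definition, which is confined to the period of ICI administration, is first reconciled with the week-48 endpoint.

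The cost is a one-page checklist at time points that already exist, some telephone calls, one data field and one further analysis with fewer events. The checklist and the field must be in place during follow-up, because unequal questioning cannot be fully repaired afterwards. The sensitivity analysis can be specified at any time before the data are analysed.

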**FIGURE 1 F1:**
[figure not shown]
Study schedule 1. Timing of ordinary samples for patients included receiving immune checkpoint inhibitors administered every 2 weeks (nivolumab, avelumab, and durvalumab). *Measurements not included in this study (potentially for use in future research projects). ANA, antinuclear antibody; RF, rheumatoid factor; ANCA, antineutrophil cytoplasmic antibody; Vit D, vitamin D (measured as 25-hydroxycholecalciferol); IL, interleukin.

**FIGURE 2 F2:**
[figure not shown]
Study schedule 2. Timing of ordinary samples for patients included receiving immune checkpoint inhibitors or combinations of immune checkpoint inhibitors administered every 3 weeks (ipilimumab + nivolumab, pembrolizumab and atezolizumab). *Measurements not included in this study (potentially for use in future research projects). ANA, antinuclear antibody; RF, rheumatoid factor; ANCA, antineutrophil cytoplasmic antibody; Vit D, vitamin D (measured as 25-hydroxycholecalciferol); IL, interleukin.

Ordinary and extraordinary samples will be analyzed together at the end of the follow-up period, once the whole cohort reaches week 48.

#### Ordinary Samples and Study Schedules

Prior to receiving the first dose of ICI, all patients will undergo a baseline (i.e., week 0) blood test for research purposes, at the same time as their baseline blood test for medical purposes.

For ICIs administered every 2 weeks (nivolumab, avelumab, and durvalumab), sequential blood tests will be performed per protocol at weeks 2, 6, 12, 24, 36 and 48 after ICI initiation, all of them at the same time as draws for medical purposes (Figure 1). In other words, four ordinary samples will be obtained in the first 12 weeks (i.e., at 0, 2, 6, and 12 weeks after ICI initiation). Thereafter, the ordinary blood sampling interval will be every 12 weeks up to the end of follow-up at week 48.

For ICIs or combinations of ICIs administered every 3 weeks (ipilimumab plus nivolumab, pembrolizumab, and atezolizumab), sequential blood tests will be performed at weeks 0, 3, 6, 12, 24, 36 and 48 after ICI initiation, all of them at the same time as draws for medical purposes (Figure 2). In other words, four ordinary samples will be obtained in the first 12 weeks (i.e., at 0, 3, 6, 12 weeks after ICI initiation). Thereafter, the ordinary blood sampling interval will be 12 weeks up to the end of follow-up at week 48.

In the event of a delay in the administration of an ICI dose due to any eventuality other than an irAE, the ordinary sample corresponding to that treatment cycle will not be obtained. If the delay is due to the occurrence of an irAE, then an extraordinary sample will be obtained, as per protocol (see “*Extraordinary samples*” in the next section). Once treatment resumes, the ordinary sample corresponding to that treatment cycle will be collected per protocol.

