#### Extraordinary samples

At the time an irAE is detected, an additional blood sample will be collected for tests including the autoantibody panel under study. At the discretion of the attending physician, screening for other more specific antibodies may be requested based on the clinical manifestations of the patient. For ethical and decision-making reasons, the results of these extraordinary analyses for medical purposes will be available to the attending physicians.

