### Laboratory Management and Sample Circuit

Both ordinary and extraordinary samples for research purposes will be separated from samples for medical purposes and will be processed to obtain six 500-μL aliquots of serum each. These aliquots will be stored at −80°C and appropriately labelled and coded in the biobank of each participating center. Ordinary samples corresponding to baseline (week 0), week 24 and week 48 will be processed to obtain peripheral blood mononuclear cells (PBMCs), which will be stored in the biobank at −80°C as cell pellets for subsequent DNA and RNA extraction.

After completion of follow-up, serum samples will be centralized in a single autoimmunity laboratory located in the Central Laboratory of Araba University Hospital (Vitoria-Gasteiz) to be analyzed by a blinded team of physicians and technicians with extensive experience in clinical laboratory testing. The panel of autoantibodies under study (ANAs, RF, and ANCAs) will be used to screen the serum from the ordinary and extraordinary samples. In some cases, the serum from the extraordinary samples obtained at the time of an irAE diagnosis may be tested for other more specific autoantibodies, at the discretion of the attending physician. In addition, vitamin D levels will be measured as 25-hydroxycholecalciferol in the serum from ordinary samples at baseline and weeks 24 and 48.

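### Research sampling depends on why a dose is delayed, so irAE patients get more looks for autoantibodies; the bias in time to appearance is small but cheap to avoid

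*Protocol article*

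**What the plan says.** All places are in the protocol article.

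- *Ordinary Samples and Study Schedules*, three-weekly schedule: "sequential blood tests will be performed at weeks 0, 3, 6, 12, 24, 36 and 48 after ICI initiation". The two-weekly schedule has week 2 in place of week 3. Each gives seven planned looks, 12 weeks apart after week 12.
- Same section, delay for a reason other than an irAE: "the ordinary sample corresponding to that treatment cycle will not be obtained".
- Same section, irAE delay: "If the delay is due to the occurrence of an irAE, then an extraordinary sample will be obtained, as per protocol".
- The sentence that follows: "Once treatment resumes, the ordinary sample corresponding to that treatment cycle will be collected per protocol". It does not say which kind of delay it covers.
- *Extraordinary samples*: "At the time an irAE is detected, an additional blood sample will be collected for tests including the autoantibody panel under study". This applies whether or not a dose is delayed.
- *Laboratory Management and Sample Circuit*: the panel "will be used to screen the serum from the ordinary and extraordinary samples". *Follow-Up Methods* adds that both types are analysed together once the cohort has reached week 48.
- *Endpoints* lists among the secondary outcomes "time to autoantibody appearance and number of positive autoantibodies included in the panel at week 48". *Secondary Objectives* compares irAE-free survival between patients positive before ICI, positive after ICI, and never positive. It also asks about early appearance up to irAE diagnosis.

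No section limits appearance, or the positive-after-initiation group, to scheduled samples. *Management of Potential Bias* deals with suspicion of irAEs in antibody-positive patients and with laboratory blinding, but not with unequal sampling.

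**The concern.** Appearance of an autoantibody is seen only when serum is drawn, so the recorded date depends on the true date and on the sampling times. Here the sampling times depend partly on the outcome. A patient with an irAE is tested on the event date. A patient without one waits for the next ordinary draw, and loses that draw if the dose happens to be delayed for another reason. Blinded assays do not correct a different number of looks.

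The delay rule is also unclear. If the resumption sentence covers irAE delays only, the reason for delay decides who keeps the scheduled sample. If it covers all delays, it contradicts the statement that the sample is not obtained. Five hospitals could apply it differently.

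At stake are time to autoantibody appearance and membership of the positive-after-initiation group. Both could differ by irAE status with no biological link.

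**Working it through.** The article gives no figure for this effect, so there is none to reproduce. Its sample-size figures (70 irAE cases, 210 without) are used only in step 5.

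**1. Looks under the written rules** (natural reading)

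- No irAE, no delay: 7.
- k non-irAE delays falling on sampling cycles: 7 − k.
- One irAE with treatment resumed, no other delay: 7 + 1 = 8.

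**2. Detection gap.** Draws fall at weeks 12, 24, 36 and 48. Without week 24 the gap is 36 − 12 = 24 weeks. Without week 48, an appearance after week 36 is never seen.

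**3. Hand calculation.** Assume appearance and irAE times uniform over 48 weeks. The gaps g on the three-weekly schedule are 3, 3, 6, 12, 12, 12.

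- Mean lag from true to seen appearance = Σg²/(2 × 48) = (9 + 9 + 36 + 3 × 144)/96 = 486/96 = 5.06 weeks.
- With week 24 dropped: (9 + 9 + 36 + 576 + 144)/96 = 774/96 = 8.06 weeks, or 3.0 weeks later in that patient. Non-irAE delays also occur in irAE patients, so this is not in itself a between-group difference.
- Mean saving from one extra draw at the irAE = Σg³/(6 × 48²) = 5454/13824 = 0.39 weeks.

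**4. Simulation with no true association** (2,000,000 patients per scenario, three-weekly schedule). The 25% irAE rate is from the article. The other inputs are assumptions: 20% appearance by week 48 at constant hazard, irAE time uniform over weeks 1 to 48, post-baseline ordinary draws missed equally often in both groups, and 0, 2 or 5% transient positivity per look. Each cell gives irAE against no irAE. Odds ratios are from unrounded output.

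| Draws missed | Mean looks | Mean lag, weeks (0% transient) | Difference | Ever-positive OR at 0 / 2 / 5% transient |
|---|---|---|---|---|
| 0% | 8.00 v 7.00 | 4.61 v 5.03 | 0.42 | 1.01 / 1.07 / 1.11 |
| 10% | 7.40 v 6.40 | 5.29 v 5.87 | 0.58 | 1.00 / 1.07 / 1.13 |
| 20% | 6.80 v 5.80 | 5.95 v 6.79 | 0.84 | 1.01 / 1.09 / 1.14 |
| 30% | 6.20 v 5.20 | 6.71 v 7.84 | 1.13 | 1.04 / 1.10 / 1.17 |

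The first row agrees with step 3 (5.03 against 5.06, and 0.42 against 0.39). With no missed draws and no transient positivity the true odds ratio is 1, because week 48 catches everyone, so the 1.01 there is simulation error. A separate run on the two-weekly schedule, with 19.2% seroconversion and 0 to 20% missed, gave odds ratios of 1.002 to 1.010 and a difference of 0.4 to 0.7 weeks.

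**5. Bias against precision**, 70 v 210 patients, for the two 30% missed scenarios at 0% and 5% transient positivity

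- 0% transient (0.185 v 0.180): SE(log OR) = √[1/(70 × 0.185 × 0.815) + 1/(210 × 0.180 × 0.820)] = 0.36. Bias is ln 1.04 = 0.04, about 0.1 SE.
- 5% transient (0.406 v 0.370): SE = √[1/(70 × 0.406 × 0.594) + 1/(210 × 0.370 × 0.630)] = 0.28. Bias is ln 1.17 = 0.16, about 0.6 SE.

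**6. Ordinary samples only.** Observed positivity then agrees between groups, for example 0.397 v 0.397 at 20% missed and 5% transient. This requires missed draws to be equally common in both groups.

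**The case against.** A reader might infer that irAE patients will look clearly more often positive, with a spurious odds ratio of about 1.3 to 1.4. Such a figure can be produced. Assume 19.2% seroconversion by week 48, and compare positivity seen by the event date in irAE patients (0.0948) with that in non-irAE patients at a matched time. The comparator is 0.0752 with no missed draws and 0.0677 with 20% missed, and the odds ratios are 1.29 and 1.44. The article does not support this as the size of the problem, for two reasons.

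- It defines no such contrast. Its groups are formed over the whole of follow-up, and time to appearance is listed without a comparison at matched event times.
- In the Discussion, 19.2% is an upper figure for some autoantibody types, from an ipilimumab-treated melanoma cohort tested with 23 autoantibodies. It has no week-48 horizon.

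Other objections stand in part.

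- The delay rule is not the main driver. Even in that contrast the ratio is 1.29 with no missed draws, so most of the effect comes from the sample taken at the irAE. This stands.
- The resumption sentence can be read as covering every delay, so that the sample is only deferred. That is possible, but it then conflicts with the preceding rule, and the extra look per irAE remains.
- The event sample is what informs early appearance up to irAE diagnosis, an objective followed within irAE patients. This stands and limits the remedy.
- Ordinary draws are tied to ICI doses, and withdrawal after an irAE could remove later ones. This stands, so the net direction is uncertain.
- An analysis plan that is not shown may choose the samples and the censoring method. It may, but it cannot recover serum that was never drawn.

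**Conclusion.** The point holds as a modest, avoidable design weakness in secondary outcomes. As written, the collection rules make the number and timing of looks depend on irAE status, and the delay wording is either unequal or contradictory.

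Under the assumed inputs and no true association, first positivity is seen 0.4 to 1.1 weeks earlier in irAE patients when positivity persists. Ever-positive status is then almost unbiased. An odds ratio near 1.17 needs the most unfavourable scenario examined, 30% missed draws and 5% transient positivity per look. Delay frequency, transient positivity and draws lost after withdrawal are not in the article, so these are illustrations and the sign could change. A large false association with irAE is not shown. The case for acting is that the collection rule cannot be repaired after follow-up and costs little to change.

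**What to change.** 1. Use one research-sampling rule for every delayed dose, whatever the reason: take the ordinary sample at the resumed dose and record its actual date. Reword the delay paragraph so that its sentences agree.
2. For comparisons between irAE and non-irAE patients (time to appearance, positive-after-initiation group), define first positivity from ordinary samples. Treat it as interval-censored between the last negative and first positive sample, which also allows for unequal gaps.
3. Keep extraordinary samples for the objective on appearance up to irAE diagnosis, and report them separately.

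The cost is a few more serum tubes at visits that take place anyway, a change of wording, an interval-censored analysis, and some loss of timing detail in the between-group comparison. The sample size of 294 and patient treatment do not change. Sampling at the resumed dose does not help patients who never resume, so the number of ordinary draws obtained should be reported by irAE status.
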